##### Women’s surveys and interviews

Women aged 14 years and over, pregnant with a First Nations baby and booked for maternity care in either research setting are eligible to participate. Of women in the new care models, we estimate approximately 50% will complete the pregnancy survey. From that group, we estimate based on our previous work, a 70% response rate at 2-months postpartum and a 50% response rate at 6-months postpartum. Of the women recruited to participate in surveys, we estimate approximately 10% will be interviewed.

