#### Data collection procedures

##### *Women’s surveys*

Survey data collected at three time points will be used to assess outcomes (including women’s experiences) against study aims. There will be the option of completing surveys independently online or with a researcher. Surveys will include questions related to many aspects of maternity care, as well as general life circumstances (e.g. social, emotional, demographic), and other factors such as cultural identity and connection (see Table 2). Surveys are based on previous research work and include relevant validated instruments that have been used by our team previously (see Additional File 2 for scales and tools to be used).

Piloting and early data collection from the IBUS study identified that most women complete the surveys online, while some were receptive to face-to-face completion with researchers entering data directly into a device or being nearby to answer queries during completion. All jurisdictional restrictions for the COVID-19 pandemic will be followed, and additional precautions will reduce risks to participants and researchers (e.g. mask wearing). Where allowable, options will be offered regarding a meeting place of the participants’ choosing. A $20 grocery/department store gift card will be provided after each survey completion, and a small baby gift will be given following the 2-month survey.

When women complete a survey with a researcher, full verbal explanations will be provided. If a survey response(s) indicates a service issue, with the participant’s permission this may be escalated for further action. Researchers will be aware of local hospitals’ complaints processes, and may help or arrange assistance with this. Where online surveys are completed, and a high score and/or selection of ‘trigger’ responses on particular scales are recorded e.g. the Edinburgh Depression Scale (EDS), designated researchers will receive an immediate alert email. Participants will be offered referral (as per IBUS procedures), and triggers and follow ups will be documented.

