##### Women’s surveys

Participation in BOOSt research will be encouraged utilising multiple approaches, including face-to-face, and online dissemination, where we aim for maximum awareness at both study sites. Front line health staff will be engaged in dissemination of information (e.g. flyers), inviting potential eligible participants to submit an ‘Expression of Interest’ (EOI) for researcher contact.

Eligible women will be recruited in the third trimester (approximately 28–36 weeks gestation) to complete surveys. This will involve three surveys: during pregnancy, approximately 2 months and 6 months after birth. Women who have already given birth to a First Nations baby in the past 6 months, are also able to participate, by completing the relevant survey. These women will have the option to retrospectively complete earlier questionnaires pending discussion with a researcher. The limitations, risks and benefits of this approach are recognised.

Following relevant ethics guidelines [64], women will be advised they may defer a participation decision until they have had an opportunity to discuss with a trusted person(s). Any questions will be answered. For participants recruited to complete questionnaires, consent will be acquired for the use of routinely collected electronic health records data, and for merging of records with participants’ survey data. Other service user groups whose de-identified data will be analysed in the study will not be asked for consent, as this research meets conditions stipulated in the National Statement for waiver of consent^4^ [63].

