#### Quantitative data

##### Health services and other routinely collected data

Anonymous data from all women attending the site hospitals and health services during the study period will be extracted and analysed by birth model of care. Quantitative analyses will compare maternal and infant health outcomes between the baseline cohort (both sites) and Birthing on Country service innovation cohort (both sites), as well as standard care/concurrent and historical control groups, and non-First Nations groups (where available).

The clinical and costing outcomes data will be derived from routinely collected electronic healthcare databases at each site. Data will be imported to Stata® or Statistical Package for Social Sciences (SPSS®). While data will initially be re-identifiable (with unique study number) all patient identifiers will be removed. Data cleaning and coding decisions will be documented.

Analysis will be performed with the latest version of the appropriate software and statistical significance will be determined at the 0.05 level. Binary outcome measures will be presented using odds ratios with 95% confidence intervals. Several methods will be used to address selection bias e.g. multivariate logistic regression models, linear regression models, propensity score matching (identifies and controls for confounders e.g. the presence of pregnancy complications), and multilevel modelling controlling for clustering factors. Longitudinal outcomes will be analysed with generalized estimating equations to account for the correlation between observations repeated in the same person. We will use trend analysis to compare rates of preterm birth between First Nations and non-First Nations women, which will demonstrate if this inequity has reduced.

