##### Survey data

Survey data will usually be entered at point of collection directly into the Qualtrics® platform by the research participant or researcher. Once recruitment has closed, data will be extracted from Qualtrics® and imported into SPSS® or Stata®. Descriptive analysis will be performed. Additionally, re-identifiable survey data in Stata®/SPSS® (with unique study number) will be merged with clinical data for further analysis. Analysis will compare outcomes from the baseline cohorts and implementation cohorts (both sites). Descriptive statistics will highlight relevant rates, ratios and percentages/proportions.

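### Recalled pregnancy questionnaires, and GEE with about 25% of women expected to respond at 6 months, put the longitudinal survey outcomes at risk of bias

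*Protocol article*

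**What the plan says.** **Method.** The protocol article, under Quantitative data (Health services and other routinely collected data), says: "Longitudinal outcomes will be analysed with generalized estimating equations to account for the correlation between observations repeated in the same person". It states no working correlation, weights or missing-data rule. Under Survey data it says "Descriptive analysis will be performed" and adds a comparison of baseline and implementation cohorts, with further analysis after merging with clinical data. Under Data collection procedures it says: "Survey data collected at three time points will be used to assess outcomes".

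**What is repeated.** Table 2 schedules these outcomes more than once:
- K5 at 36 weeks, 2 months and 6 months
- Negative Life Events Scale at 36 weeks and 6 months
- EPDS at the first antenatal visit, 2 months and 6 months
- breastfeeding status at 2 and 6 months

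**Expected response.** Women's surveys and interviews says: "Of women in the new care models, we estimate approximately 50% will complete the pregnancy survey". Of that group it expects "a 70% response rate at 2-months postpartum and a 50% response rate at 6-months postpartum".

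**Recall.** The recruitment section on women's surveys admits women who gave birth within the previous 6 months. It continues: "These women will have the option to retrospectively complete earlier questionnaires pending discussion with a researcher". The next sentence is "The limitations, risks and benefits of this approach are recognised". No rule marks or separates such questionnaires. The same section obtains consent to link survey participants' health records.

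**The concern.** Two stated choices meet in the same data.

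First, the K5 measures psychological distress as a current state. A 36-week K5 completed after the birth is not a 36-week measurement. The birth and the care received may colour it, and these are what the new service is meant to change. Because the option covers earlier questionnaires in general, a woman who joins late could also recall the 2-month wave.

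Second, response is expected to fall steeply between waves. GEE without weights is in general assured valid only if drop-out is completely at random or depends only on covariates in the model. If drop-out depends on earlier or current scores, the means at each wave and the changes between waves can be wrong. If that dependence differs between models of care, the group comparison can be wrong too. Table 1 makes a difference conceivable, since contact with a named midwife until 6 weeks after birth is part of one model and not the other.

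At stake are the secondary wellbeing outcomes. The primary outcomes are antenatal attendance, birth and discharge measures and do not depend on the surveys.

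**Working it through.** The article derives no power or bias figure for the survey outcomes, so there is none to reproduce.

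**1. Expected respondents in the innovation cohorts.** Inputs are the minimum births in Power and sample sizes (296 rural, 264 urban) and the response rates quoted above. Births are treated as women.

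| Site | Births | Pregnancy (× 0.5) | 2 months (× 0.7 of pregnancy) | 6 months (× 0.5 of pregnancy) |
|---|---|---|---|---|
| Rural | 296 | 148 | 104 | 74 |
| Urban | 264 | 132 | 92 | 66 |
| Both | 560 | 280 | 196 | 140 |

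The 6-month share is 0.5 × 0.5 = 25%, or 140/560. Women recruited after birth would add to the postnatal counts; the article does not say how many.

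**2. Drop-out.** A simulation used 40,000 women in two groups and three waves, with equal true means, SD 1 and response of 100%, 70% and 50%. Assumed, not in the documents: within-woman correlation 0.6, and odds of non-response multiplied by 1.5 or 2.0 per SD of score. Drop-out depended either on the first-wave score (missing at random) or on the outcome itself (missing not at random). The true change is 0.

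Bias in the change to 6 months, in SD, with the same mechanism in both groups:

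| Drop-out | Odds ratio per SD | GEE, independence | GEE, exchangeable | Inverse-probability weighted |
|---|---|---|---|---|
| Completely at random | 1.0 | 0.001 | 0.004 | not run |
| At random | 1.5 | −0.119 | −0.001 | 0.000 |
| At random | 2.0 | −0.174 | 0.007 | 0.006 |
| Not at random | 1.5 | −0.180 | −0.104 | not run |
| Not at random | 2.0 | −0.321 | −0.198 | not run |

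The negative sign follows from the assumption that women with higher scores drop out more.

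With the same mechanism in both groups, the between-group difference in change stayed between −0.025 and 0.026 SD. That is simulation noise: the completely-at-random runs gave −0.014 to 0.028. With score-dependent drop-out in one group only, the bias in that difference was:

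| Drop-out | Odds ratio per SD | GEE, independence | GEE, exchangeable | Inverse-probability weighted |
|---|---|---|---|---|
| At random | 1.5 | −0.137 | −0.017 | −0.016 |
| At random | 2.0 | −0.199 | 0.000 | 0.001 |
| Not at random | 1.5 | −0.199 | −0.117 | not run |
| Not at random | 2.0 | −0.297 | −0.176 | not run |

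**3. How far an exchangeable correlation can be trusted.** It removed the missing-at-random bias above because it was correctly specified and the outcome was normal. In a further run with correlation decaying over time (0.7, then 0.4), exchangeable GEE was off by 0.04 to 0.07 SD. With a dichotomised score and drop-out driven by the underlying score, the bias was −0.07 to −0.21 in log odds, an odds ratio of 0.93 to 0.81 where the truth is 1.

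**4. Recall.** Bias in the pregnancy-wave mean = share recalled × recall shift. With an assumed share of 10% to 30% and shift of 0.1 to 0.5 SD, it runs from 0.10 × 0.1 = 0.01 SD to 0.30 × 0.5 = 0.15 SD. Change from pregnancy carries the same error with the opposite sign.

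**The case against.** The article does not say that the GEE will be unweighted. Working correlation, weights and missing-data rules are commonly left to an analysis plan, so their absence is no finding, and weighted GEE would satisfy the quoted sentence. This stands. The point is that the method as named does not by itself protect against the drop-out that the article forecasts.

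A reader might infer that the survey results will be biased, and that postnatal wellbeing will look better than it is. The documents do not support that. Nothing in them links non-response to distress, and response rates are forecast only for the new care models. A correctly specified exchangeable GEE is about unbiased under missing at random with a normal outcome, and drop-out that acts alike in both groups roughly cancels in the comparison.

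A reader might also infer that recall spoils a baseline measurement. The article never gives the 36-week survey that role. Its baseline is the standard-care cohort, and it counts exposure from the start of pregnancy. The EPDS is little exposed to recall, since its antenatal score belongs to the first visit and medical records are one source.

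The GEE sentence sits under routine data, so its application to survey scales is a reading of the text. It is the natural one, because the outcomes that Table 2 repeats are mainly survey scales.

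Finally, retrospective completion is optional and case by case, and the article acknowledges its limits. But acknowledging them does not keep recalled scores out of the pregnancy wave, and a flag not captured at collection may be impossible to rebuild at analysis.

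**Conclusion.** The concern holds as a risk of bias in secondary outcomes. The stated recall option places post-birth answers on state scales in the pregnancy wave. The stated method, used without weights, needs stronger drop-out assumptions than a likelihood-based or weighted analysis that the linked data already allow. About 25% of women in the new models are expected at 6 months.

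Size and direction cannot be fixed from the documents. On the assumptions shown, bias in the 6-month change is between about 0 and 0.32 SD, depending on mechanism and working correlation. In the comparison of models of care it is about 0 if drop-out acts alike in both groups, and up to about 0.30 SD if it depends on the outcome in one group only. Recall adds 0.01 to 0.15 SD to the pregnancy-wave mean under assumed shares and shifts. The primary outcomes are unaffected.

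**What to change.** 1. Record at collection, for each questionnaire, whether it was completed retrospectively.
2. Exclude recalled state-scale scores (e.g. K5) from the main longitudinal model, with a sensitivity analysis that includes them.
3. Specify a likelihood-based mixed model, or GEE weighted by inverse probability of response, with weights built from earlier survey scores and the linked clinical records. State that neither cures drop-out that is missing not at random.

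The cost is one extra data item, a change of analysis wording and modest programming. The downside is slightly wider intervals and fewer pregnancy-wave scores. Item 1 is the urgent one because it must be in place while surveys are being collected.

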##### Survey data

Survey data will usually be entered at point of collection directly into the Qualtrics® platform by the research participant or researcher. Once recruitment has closed, data will be extracted from Qualtrics® and imported into SPSS® or Stata®. Descriptive analysis will be performed. Additionally, re-identifiable survey data in Stata®/SPSS® (with unique study number) will be merged with clinical data for further analysis. Analysis will compare outcomes from the baseline cohorts and implementation cohorts (both sites). Descriptive statistics will highlight relevant rates, ratios and percentages/proportions.

#### Qualitative and sustainability data

 The research team will manage transfer, transcription and analysis of in-depth interview and yarning circle data. Data collected through digital audio-recorder systems will be saved in the restricted access Sharepoint. Original audio files will then be deleted from devices.

For analysis of the de-identified qualitative data, we anticipate using thematic analysis and culturally-relevant narrative analysis methods as appropriate for yarning [51] and narrative inquiry. Data will be imported and managed in the latest version of NVivo® (QSR International), where a five step process will be undertaken for thematic analysis: (i) immersion in the raw data (ii) identification of a thematic framework (coding scheme) (iii) application and modification of the framework (incorporates revision and refining of coding scheme based on emergence of new themes) (iv) abstraction and synthesis of themes into higher level categories (v) development of association between categories with a view to explaining findings [65]. Any overlap, inconsistencies and outliers in the analysis are to be reconciled; and a final coding scheme confirmed. Standard practice is for interviewees to be assigned a pseudonym and any other uniquely identifying details removed prior to publication. We recognise some of our partners may actually wish to be named [66] which will be offered as appropriate.

Progress reports will be circulated to key investigators as part of the PAR process. Findings will be used iteratively where possible to inform ongoing development of the Birthing on Country services. Steering committees will consider issues or concerns. Investigators and the research team will meet at least annually to provide guidance on study progress. Researcher field notes will be recorded and saved as text files. These documents will be accessed for content and/or thematic analysis.

All data acquired regarding service sustainability will be analysed according to data type. Our team are currently using the RISE Framework [21, 67] and Realist approaches to evaluate the BiOC service (forthcoming).

#### Participant database

 A purpose-built, participant log sheet will be password-protected and secured with restricted access. The file will contain participant contact details for longitudinal follow-up and unique study numbers**.** All paper-based documents will be stored in locked cabinets. Anonymous identifying information will be extracted from each site’s database to enable the creation of a merged mother and infant record using all data sources and a unique study number. Data subsets will also be extracted for blinded analysis.

## Discussion

The BOOSt study will explore the feasibility of establishing two new Birthing on Country services inclusive of a birth centre, in diverse settings, and the processes required to ensure sustainability. BOOSt will investigate clinical effectiveness, cultural safety, costs and cost-effectiveness of these services alongside the acceptability of services for women and families, Communities and health service providers. The BOOSt partnership brings together a unique and multidisciplinary team to enable a novel and strategic approach to health services innovation, which we propose, has the potential to profoundly and positively impact health and wellbeing outcomes for First Nations women, infants and families.

The BOOSt study’s innovative approach draws on evidence from other countries and settings. The partnership will work with First Nations women, Communities and leaders, to make an impact. BOOSt will set a new standard for the provision of First Nations-led and culturally safe maternity care and will offer an evidence-based model for future adaptation. Translating research outcomes requires effective cooperation to enable transfer and take up. ACCHOs will provide the framework for engaging with First Nations women, and will ensure vital knowledge for translating findings for Communities and other interested parties.

## Ethical considerations

This research complies with all relevant national, international and local guidelines and has been approved by Ethics Committees (as listed) including the Aboriginal Health & Medical Research Council (AH&MRC, NSW) Ethics Committee (1448/18). We prioritise respect for the dignity and wellbeing of women and other study participants, and sound project oversight and governance are in place. Relevant procedures have been reproduced and adapted from IBUS.

## Dissemination of results and publications

We will adhere to first principles meaning First Nations voices, lived experiences, interpretations, and considerations will be privileged in all processes. Dissemination activities will occur in consultation and collaboration with our partners.

## Data Availability

Data sharing not applicable to this article as no datasets were generated or analysed during the current study. The questionnaires/data collection tools may be made available on request and/or may be included with future publications of data/findings.

## Abbreviations

ACCHO: Aboriginal Community Controlled Health Organisation
AH&MRC: Aboriginal Health & Medical Research Council (of NSW)
ANC: Antenatal Care
ATSICHS: Aboriginal and Torres Strait Islander Community Health Service Brisbane Ltd.
BiOC: Birthing in Our Community
BoC: Birthing on Country
BOOSt: Building On Our Strengths
Community/ies: Capital C denotes reference to First Nations Community/ies rather than reference to the community in general
IBUS: Indigenous Birthing in an Urban Setting
IUIH: Institute for Urban Indigenous Health
MGP: Midwifery Group Practice
NHMRC: National Health & Medical Research Council (Australia)
NSW: New South Wales (State Jurisdiction)
PAR: Participatory Action Research
PICF: Participant Information and Consent Form
QLD: Queensland (State Jurisdiction)
SDMH: Shoalhaven District Memorial Hospital
